## Abstract

**Study design:**

A two parallel group exploratory single center feasibility randomised controlled trial. A nested qualitative study will explore the acceptability of the study processes and patient and physiotherapists experiences of the interventions.

**Objectives:**

The aim of this trial is to test the feasibility of undertaking an RCT investigating the effectiveness of a mult- component structured physical rehabilitation intervention aimed at reducing physical disability in adults with mild stable DCM compared with clinical surveillance.

**Setting:**

The study will take place in the national neurosurgical centre in Dublin, Ireland.

**Methods:**

A two parallel group exploratory single center feasibility RCT with will recruit 24 people with mild stable DCM from the outpatient clinics of a tertiary neurosurgical referral service. A nested qualitative study will explore the acceptability of the study processes and patient and physiotherapist experiences of the interventions. The intervention will include education, a physical activity behavioural change intervention, cervical range of motion exercises, neck, upper limb and scapular strengthening exercises and task specific hand function training. The primary outcomes are the feasibility of recruitment, adherence, and retention. The secondary outcomes which will be completed at baseline and 12 weeks follow up are the DCM core outcome set and an NRS for neck and arm pain.

**Conclusion:**

Developing novel rehabilitation interventions for people with DCM is the sixth most important research priority in the field of DCM. The findings from this feasibility RCT will inform the feasibility and design of a future definitive RCT.

## Introduction

Degenerative cervical myelopathy (DCM) is a standard unifying term for cervical myelopathy, the most common type of non-traumatic spinal cord injury, which occurs secondary to degenerative and or congenital changes to the structure of the spinal column [1]. The most up to date clinical practice guideline recommends surgical intervention for people with moderate or severe DCM, progressive DCM or those at high risk of progression [2]. The guideline also suggest that people with mild DCM should be offered surgery or a supervised trial of structured rehabilitation [2]. The recommendatons for people with mild DCM are based on low to very low quality evidence [3].

The decision to proceed with surgical intervention in mild DCM is conflicted due to the limited data available on the natural history of mild DCM [4], evidence that surgery is associated with at best small improvements in mild DCM [5–7] and the risk of a surgery related complicaton is high, irrespective of disease severity [6, 7]. To date, there have been no high quality studies investigating alternatives to surgery in DCM including rehabilitation [8]. An international multi-stakeholder research priority setting partnership has established that developing novel rehabilitation interventions for people with DCM both as a primary intervention or as an adjunct to surgery is the sixth most important research priority in the field of DCM [9].

People with mild DCM typically present with neck pain, neck stiffness, upper limb weakness and dexterity loss. There is evidence from other comparable clinical populations (i.e. stroke, traumatic spinal cord injury and cervical radiculopathy) that rehabilitation has the potential to deliver clinically important improvements in neck pain and related disability and upper limb function [10, 11]. Before an adequately powered RCT can be designed for mild DCM, the feasibility of participant recruitment and retention must be established, the interventions must be refined, the safety and outcome of the proposed physical rehabilitation intervention explored, and a sample size calculated [12]. Clinical surveillance is the current standard of care for people with mild DCM who have not reached the threshold for surgery or have elected to proceed with non-operative care. Therefore, clinical surveillance has been chosen as the comparator intervention in this trial. Therefore, the aim of this trial is to test the feasibility of undertaking a RCT investigating the effectivess of a physical rehabilitation intervention compared to clinical surveillance in adults with mild stable DCM.

## Objectives

The primary objectives are [1] to confirm the incidence of mild stable DCM in the neurosurgical outpatient clinics, [2] to assess the eligibility rate of people with mild stable DCM (defined as no worsening of neurological symptoms x 3 months), [3] to assess the participation rate of those eligible, [4] to establish participant and clinician adherence to the intervention and the acceptability of the interventions to participants and clinicians and [5] to determine participant retention, and the acceptability of the proposed outcome measures by measuring the proportion of patients providing complete outcome data at 12 weeks and the burden of measurement tool completion. The secondary objectives are [1] to describe changes and estimate variability in clinical outcomes to inform the sample size and design of a future effectiveness study and [2] to conduct a process evaluation according to Medical Research Council guidelines to assess fidelity and quality of implementation and clarify causal mechanisms [13].

### Trial design

This trial is a two parallel group exploratory single center feasibility randomised controlled trial (Fig. 1). A nested qualitative study will explore the acceptability of the intervention to both participants and the treating physiotherapist using the theoretical framework of acceptability [13, 14]. The updated medical research council (UK) framework for developing and evaluating complex intervention was used in the development of this intervention[15]. The standard protocol Items: recommendations for interventional trials statement [16] and the template for intervention description and replication (TIDieR) checklist and guide [17] were used in the preparation of this protocol. This feasibility trial has been registered on clinicaltrial.gov (NCT06781658).

**Fig. 1 Fig1:**
[figure not shown]
Sample participant flow diagram following CONSORT guidelines. This diagram shows the propsed flow of participants in the ReMiDY feasibility RCT and the data on recruitment, randomisation, retention and analysis that will be reported.

### Study setting

The study will take place in the Department of Neurosurgery in Beaumont Hospital which is large urban academic teaching hospital in Dublin, Ireland. Beaumont Hospital is the national referral service for neurosurgery and a regional spinal surgical service.

### Eligibility criteria

**The inclusion criteria are:**
Participants aged ≥18 years.Diagnosis of DCM (Clinical symptom of DCM + upper motor neuron sign + imaging evidence of cervical cord compression). Diagnosis will be confirmed by a consultant neurosurgeon [18].Modified Japanese Orthopaedic assessment (mJOA) score of 15-17, indicating mild DCM. The mJOA is a clinician administered validated measure of DCM severity [19].Adequate comprehension of English to understand the purpose of the study and give written informed consent

**The exclusion criteria are:**
Patient or surgeon preference for urgent surgical decompression for progressive DCM, motor radiculopathy or severe unrelenting radicular arm pain or significant risk factors for progression including co-existing cervical radiculopathy and circumferential cord compression.Diagnosis of other neurological condition that could confound assessment.Involvement in another clinical study or trial.Pregnancy.If the participant is unable to commit to a 12-week programme of up to 10 sessions of supervised physical rehabilitation and participating in a regular home exercise programme for the duration of the study.

## Recruitment

Recruitment to the trial will be via the neurosurgical outpatient clinics in Beaumont Hospital. All new outpatient spinal referral letters to five consultant neurosurgeons who accept outpatient spinal referrals will be screened for any clinical or imaging evidence suggestive of DCM by the research team prior to the patients attending for their first assessment. The patient will then attend for their neurosurgical consultation where they will be screened for DCM and have a myelopathy severity index completed as part of their usual care.

If a patient is diagnosed with mild stable DCM at their neurosurgical clinic outpatient appointment and the surgical team and patient have made a shared decision to trial non operative care they will be advised about the study by their treating clinician and provided with a participant information leaflet. The patient’s verbal consent will be sought for a member of the research team to contact them by phone after a 48-h cooling-off period. A two-step screening process will be used to determine eligibility including a telephone screen, followed by a a face-to-face appointment with the researcher who is an experienced specialist physiotherapist in neurosurgery to facilitate the completion of their eligibility check, where they will have the opportunity to ask questions and, if willing to proceed, to sign informed consent. Baseline data will be collected at their first appointment with the study researcher. The baseline data will include all the relevant components of the DCM core data set and the ASIA/ISCoS international standards for neurological classification of spinal cord injury.

The revised physical activity readiness questionnaire will be used to identify any health-related risks of exercising that would require a participant to consult their general practitioner prior to participating in the physical rehabilitation intervention [20].

## Interventions

Participants in both groups will receive standardised verbal and written education on the natural history of DCM and indicators of neurological deterioration with clear instructions on how to contact their surgical team if they experience any neurological deterioration. They will be advised not to have any cervical spine manipulation or mobilisations undertaken due to the associated risk of spinal cord injury in people with established central canal stenosis [21]. They may seek other health care services, and they will be asked to record any contact with other healthcare services for their neck and upper limb symptoms on a logbook while they are enrolled in the trial.

## Clinical surveillance

Participants assigned to the clinical surveillance control group will be invited to attend a single, one to one education session which will be supplemented with a written patient information booklet after which they will be scheduled for a 12 week follow up.

## Structured Physical Rehabilitation

### Rationale and development of the intervention

The physical intervention is targeting the patient specific physical impairments and physical disability which occur secondary to DCM. Dynamic MRI, cadaveric, clinical, and biomechanical studies have been used to inform the design of the physical rehabilitation intervention as well as exercise prescription guidelines.

Participants will be prescribed a multi-component intervention which will include education, cervical range of motion exercises, progressive neck strengthening exercises, individualised scapular and upper limb strengthening, task specific hand function training and a physical activity behavioural change intervention. The TIDieR checklist has been used to provide a comprehensive description of this complex intervention [17]. The scientific rationale, prescription guidelines and dosage of each component of the intervention and a detailed description of the equipment, infrastructure, personnel and logistics involved in delivering this intervention are described in the supplementary material (Appendix C).

## Outcomes

Table 1 describes the primary and secondary outcomes and the mediators of change.

**Table 1 Tab1:** Primary and secondary outcomes and mediators of change.

Primary	Secondary	Mediators of change
• Incidence of mild stable DCM in the neurosurgical OPD clinics. • The proportion of people with mild stable DCM who meet the eligibility criteria. • Recruitment rate (per month). • Participant and clinician adherence to the physical rehabilitation intervention. • Acceptability of the intervention to the participants and clinicians. • Burden of measurement tool completion. • Participant retention.	• Physical functioning (Physical component score of the Short Form 36). • Myelopathy severity (mJOA). • Neck pain related disability (Neck disability index). • Neck pain and arm pain severity (numerical rating scale). • Spinal adverse event (spinal adverse events severity scale).	• Cervical Range of motion • Manual dexterity (9 Hole peg test) • Grip strength • Neck Strength • Free living physical activity. • Timed up and go test

*DCM* degenerative cervical myelopathy, *OPD* outpatient department, *mJOA* modified japanese orthopedic association scoring system.

## Outcomes

Appendix A provides a detailed description of the measurement tools, specific measurement variables, analysis metrics, method of aggregation, time point for each measurement and explanation of clinical relevance of all the primary and secondary outcomes and the mediators of change. It also includes the COSMIN criteria for the secondary outcomes. The following methods will be used to standardise the collection of the mediators of change:

## Cervical Range of motion

Standardised testing procedures will be used to measure active CROM in flexion/ extension, side flexion and rotation using the CROM3 device (Performance Attainment Associates, USA). This study will use the testing procedure reported in a previous high quality study which demonstrated good intra-rater reliability when the measurements were conducted by an experienced clinician in people with neck pain [22]. These will include a standardised starting position, instructions to participants, number of practice repetitions, how the range is recorded and the use of verbal and manual cues by the assessor. The CROM has also demonstrated excellent criterion validity for measuring cervical ROM in the sagittal, frontal and horizontal plane when compared to a non-invasive optoelectronic motion measurement system [23].

## Cervical strength assessment

Cervical muscle strength will be assessed with hand held dynamometry “make tests” which are isometric hold tests where the participant cannot move the resisting force. This study will employ the testing procedure from a previous high quality study which demonstrated excellent intra rater reliability in normal subjects, as no study has investigated the intra rater reliability of hand held dynamometry in people with neck pain or in patients with cervical spine structural pathology [24, 25].

The participants will be tested in the supine position for flexion and side flexion and the prone position for extension. The test procedure will consist of three isometric contractions held for three seconds for cervical flexion, extension and right and left side flexion. A 30-second rest will be given between each contraction. The first of the three contractions for each motion will be submaximal (50% of maximal effort) to give the participant an opportunity to become acquainted with the motion. Two maximal contractions will then be performed, and the peak force of both maximal contractions will be recorded. Consistent procedures will be used for placing the dynamometer. The dynamometer will be centred on the forehead just superior to the eyebrows for flexion tests. For extension, it will be positioned slightly superior to the external occipital protuberance. To test right and left side bending, the pad or strap will be placed on the lateral aspect of the head just superior to the ear. The force values will be normalized to body weight (BW). The normalized force values from the two maximal effort tests will be averaged and used for analysis.

## Manual dexterity assessment

The nine hole peg test will be used to assess manual dexterity. It is the recommended manual dexterity measure in the National Institutes of Health (NIH) toolbox for the assessment of neurological and behavioral function. It has excellent intra-rater reliability when investigated in a large sample of normal people across the age span and in other neurological conditions [26, 27]. Its reliability has not been specifically assessed in people with DCM or spinal cord injury. Testing will follow a standardised protocol which will control the positioning of the test and the testing procedure. The score will be the total time in seconds to complete the task. Participants will complete a practice trial plus two-timed trials starting with their dominant hand. Total time in seconds to complete a trial will be recorded and the average of the two trials will be used.

## Grip strength measurement

Details of the dominant hand and the most affected limb will be recorded. The American society of hand therapists protocol for hand grip assessment will be used to standardise the assessment of hand grip strength [28]. Although the reliability of hand grip strength assessment has not been assessed in a DCM specific population, a systematic review and meta-analysis has reported excellent reliability in people with upper extremity and neurological conditions [29]. This testing protocol will specify the dynamometer, body position, instructions to participants, number of practice trials and number of trials performed [28]. Both maximum and mean grip strength will be reported.

## Free living physical activity

All participants will be asked to wear a wrist-worn triaxial accelerometer (Axivity AX3, Open Lab, Newcastle) for at least 4 days. The accelerometer will record how many minutes per day each participant is sedentary and engages in light, moderate and vigorous physical activities. This study will explore the change in average minutes of sedentary behaviour and physical activity before and after the intervention.

## Timed up and go test

The timed “Up & Go” will measure in seconds, the time taken by a participant to stand up from a standard armchair (approximate seat height of 46 cm), walk three meters, turn, walk back to the chair, and sit down again. The participant will wear their regular footwear. No physical assistance will be given. They will start with their backs against the chair with their arms resting on the chair’s arms. They will be in-structed that, on the word go,” they should get up and walk at a comfortable and safe pace to a line on the floor three meters away, turn, return to the chair, and sit down again. The participants will walk through the test once before being timed to become familiar with the test. The time taken to perform the test in seconds will be recorded [30]. A previous study has investigated the electromyographic characteristics, kinetics and kinematics of gait impairment in a cohort of people with moderate to severe cervical spondylotic myelopathy (CSM) compared to healthy controls ([31, 32]. They reported a specific altered motor strategy in people with CSM which indicated that paresis was a likely underlying contributor to their gait impairment. The results of these studies also suggested that balance impairment may contribute to the gait abnormalities seen in DCM. Therefore, this study will use the” Timed up and Go test” as a lower limb functional physical performance test which is influenced by lower limb strength, balance and walking speed. Although the psychometric properties of the “TUG” have not been investigated in DCM, previous studies have reported excellent intra rater and inter-rater reliability in ambulatory people with motor incomplete spinal cord injuries and other neurological populations [33]. The “TUG” is a valid measure of functional independence in ambulatory people with incomplete spinal cord injuries [34]. In addition, the “TUG “correlates more strongly with the walking index for spinal cord injury which is a validated measure of walking in spinal cord injury than a timed walk test [35].

## Participant Timeline

The baseline variables include all the relevant elements of the DCM core data and outcome set [36]. Participant will be followed up at 12 weeks post randomisation.

## Imaging variables

The recently published core outcome and data set for DCM clinical studies specifies several imaging parameters that should be reported in DCM clinical studies [36]. These include the use of MRI and CT imaging in the patient assessment, the level(s) of compression, pathology causing compression, amount of cord compression, presence of cord signal change, the presence or absence of a spinal cord syrinx, spondylolisthesis and radiological stability. They have also specified that adjacent segment degeneration and cervical spinal alignment should also be captured as core outcomes however these two variables are not relevant for patients managed non operatively [36]. The ReMiDy feasibility study will focus on MRI characteristics which can be assessed using valid and reliable methods as patients with mild stable DCM who are being managed non operatively do not always have dynamic radiographs undertaken as part of their routine neurosurgical care. Supine MRI does not provide a valid assessment of radiological stability, cervical spine alignment or spondylolisthesis and therefore these parameters will not be collected as part of this study.

This feasibility study will record the number of recruited patients who had a CT scan, MRI scan and dynamic radiographs undertaken as part of their neurosurgical assessment. The baseline imaging variables will be reported by a radiologist from MRI scans using the methodology described in Appendix B.

## Sample size

The investigators are aiming to recruit a total of 24 participants: 12 in the physical rehabilitation intervention group and 12 in the clinical surveillance group. Previous research has identified an incidence rate of approximately seven percent of people with mild DCM among new referrals for cervical degenerative pathology to the neurosurgical unit [37]. The justifications for the sample size include both feasibility and the gains in the precision about the mean for every unit increase in the sample size per group and the gain in precision around the variance for each gain in the degrees of freedom [38]. For the nested qualitative study, purposive sampling of both clinicians and a variety of participants will be used until data saturation [39].

## Sequence Generation

Simple randomisation will be used to generate the allocation sequence. It will be generated by an independent researcher using a computer-generated randomisation schedule.

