### Statistical analysis

Statistical analysis will be performed using STATA (Version 19) software.

The data will be checked for normality, then appropriate descriptive analyses will be used to summarise participant characteristics and outcomes. Feasibility, the primary outcome of this study, will be evaluated by calculating the following recruitment, adherence, and retention metrics:Incident rate of mild DCM in new referrals to the neurosurgical outpatient clinic (reported per month of recruitment period).The proportion of people with mild DCM who were eligible for enrolment.The proportion of eligible people who consented to participate.The proportion of participants who attended their 12 week follow up in both intervention groups.The proportion of participants who attended their scheduled physiotherapy sessions in the physical rehabilitation group.The number of core intervention components included in each treatment session.

The quantitative process data will be analysed before trial outcomes to avoid bias interpretation[13]. Intervention effects will be represented by point estimates and their standard deviations. Confidence intervals will be calculated and will be interpreted with regards to the minimum clinically important difference. This data will be used to estimate a sample size required for a definitive trial, if appropriate [12].

Semi-structured interviews of the participants and clinicians will be audio recorded, transcribed verbatim and analysed thematically. The interviews will map to the theoretical framework of acceptability [14]. Findings will be reported according to the COREQ guidelines for qualitative research.

A traffic light system of green (go), amber (amend) and red (stop) which will specify the recruitment, adherence, retention, and signal of efficacy criteria for progression to a main trail will be specified a priori.

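### Simple randomisation of 24 people does not secure the 12 per group on which the sample size is partly justified

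*Protocol article*

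**What the plan says.** The Sample size section of the Protocol article states: "The investigators are aiming to recruit a total of 24 participants", divided as "12 in the physical rehabilitation intervention group and 12 in the clinical surveillance group". It gives no power calculation, precision target or dropout allowance. The number rests on feasibility, on "the gains in the precision about the mean for every unit increase in the sample size per group" and on "the gain in precision around the variance for each gain in the degrees of freedom".

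Sequence Generation then says: "Simple randomisation will be used to generate the allocation sequence". The next sentence reads: "It will be generated by an independent researcher using a computer-generated randomisation schedule". No blocking, stratification, minimisation or 12/12 constraint is mentioned anywhere in the article. The trial is at a single centre (Trial design), so there is one sequence.

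Under Statistical analysis, session attendance is reported for the rehabilitation group only and 12-week attendance is reported in both groups. Adherence and retention are among the criteria for the traffic-light progression decision. Of the outcome estimates the section says: "This data will be used to estimate a sample size required for a definitive trial, if appropriate".

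**The concern.** Simple randomisation assigns each person independently, so the arm sizes are random. The sample size, however, is stated per group and partly argued per group. The article does not leave the allocation method to another document. It names one, and that method does not usually deliver the group sizes given in the section before it.

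What is at stake is the precision of quantities that come from one arm alone: adherence to the rehabilitation programme, retention in each arm, and any standard deviation estimated within an arm for planning the definitive trial. Having 24 in total does not protect these. Once the 24 have been randomised, an uneven split cannot be repaired.

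**Working it through.** **The plan's own figure.** 12 + 12 = 24, which is consistent. No error rate, effect size, standard deviation or dropout figure is given, so nothing further can be reproduced.

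**Inputs.** Total of 24 and target of 12 per group (Sample size); simple randomisation with no restriction (Sequence Generation). Assumption: allocation probability 0.5, as the equal target implies.

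**Distribution of the split.** The size X of one arm follows Binomial(24, 0.5).

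- P(12:12) = C(24,12) / 2^24 = 2,704,156 / 16,777,216 = 0.161, so P(not 12:12) = 0.839.
- P(14:10 or worse, either direction) = 2 × P(X ≤ 10) = 0.541.
- P(15:9 or worse) = 2 × P(X ≤ 9) = 0.307.
- P(16:8 or worse) = 2 × P(X ≤ 8) = 0.152.
- P(rehabilitation arm below 12) = P(X ≤ 11) = 0.419.
- P(rehabilitation arm 9 or fewer) = P(X ≤ 9) = 0.307 / 2 = 0.154.
- Expected size of the smaller arm = 10.07.

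**Effect on precision.** All quantities are in units of the outcome SD.

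- Standard error of the between-arm difference = √(1/n1 + 1/n2). At 12:12 this is √(2/12) = 0.408. At 8:16 it is √(1/8 + 1/16) = 0.433, a ratio of 1.061.
- 95% half-width for one arm's mean = t(0.975, n−1) / √n. At n = 12 this is 2.201 / √12 = 0.635.
- Upper 95% limit for one arm's SD, as a multiple of the estimate = √[(n−1) / χ²(0.025, n−1)]. At n = 12 this is √(11 / 3.816) = 1.70.

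| Split | SE of difference relative to 12:12 | Half-width, mean of smaller arm | SD upper-limit factor, smaller arm |
|---|---|---|---|
| 12:12 | 1.000 | 0.635 | 1.70 |
| 11:13 | 1.004 | 0.672 | 1.76 |
| 10:14 | 1.014 | 0.715 | 1.83 |
| 9:15 | 1.033 | 0.769 | 1.92 |
| 8:16 | 1.061 | 0.836 | 2.03 |

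Averaged over all splits, the SE ratio is 1.023. Pooled degrees of freedom are 24 − 2 = 22 whatever the split.

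**Illustration for adherence.** The 75% figure is an assumption; the article gives none. With 9 of 12 adherent the exact 95% interval is 43% to 95%. With 6 of 8 it is 35% to 97%.

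**The case against.** Simple randomisation is valid and unbiased, and the 12 per group is worded as an aim. Two parts of the justification survive an uneven split: feasibility, and the variance argument if a pooled SD with 22 degrees of freedom is used. The 84% chance of missing 12:12 also overstates the harm, because it includes 11:13, which costs 0.4% in standard error. Splits within 11 to 13 make up 46% of sequences. The risk to the rehabilitation arm is symmetric too: it is as likely to have 15 or more people as 9 or fewer, about 15% each. All of this stands, and it limits the severity.

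Blocking has a price as well. Under Allocation Concealment the enrolling investigator is also the outcome assessor, and under Blinding assessor blinding relies partly on participants not disclosing their group. With small blocks, a disclosed allocation says something about later ones; under simple randomisation it says nothing. This stands as a reason to avoid blocks of 2, but not as a reason to leave the mismatch.

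A reader might infer that an uneven split undermines the primary feasibility outcomes as a whole. The document does not support that:

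- Incidence, eligibility and recruitment rate do not depend on the split, and overall retention uses all 24.
- Acceptability is studied through interviews analysed thematically, so statistical precision is not the issue there.
- Fidelity belongs to a secondary objective.
- Retention in a small control arm would be less precise, not unusable.

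Loss to follow-up is a separate matter. The article assumes no retention rate, and restricting the randomisation would not change attrition.

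Finally, the word simple may be loose wording for a list already fixed at 12/12. If so, the text does not say it and should.

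**Conclusion.** The point holds as an inconsistency between two sections. The Sample size section fixes and partly justifies 12 per group, while Sequence Generation names a method that produces that split in about one sequence in six and a 14:10 or worse split in more than half. There is no bias, and the loss for the between-arm comparison is small. The real cost is wider intervals for arm-specific figures: in the smaller arm, the half-width for a mean is about 21% wider at 9 people than at 12 (0.769 / 0.635 = 1.21) and about 32% wider at 8 (0.836 / 0.635 = 1.32). These results assume equal allocation probability, all 24 people randomised and, for the half-widths, approximately normal outcomes. For a feasibility trial with no power or precision target, the severity is minor to moderate.

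**What to change.** In Sequence Generation, replace simple randomisation with a concealed, restricted 1:1 scheme that the independent researcher generates and holds. Either of these would do:

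- **A random allocation rule fixed at 12/12.** This gives the stated split exactly if all 24 are randomised. The last allocations become predictable to anyone who knows the earlier ones, and balance is not assured if recruitment stops early.
- **Permuted blocks of randomly varying size, for example 4 and 6.** Avoid blocks of 2, and do not disclose the sizes to the enrolling assessor or the treating physiotherapists. Completed blocks hold an even number of people, so at 24 randomised an incomplete last block holds 2 or 4. The arms then differ by at most 2, which is 13:11 at worst.

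The cost is one revised sentence and a regenerated list, with slight predictability of late allocations as the downside.

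If simple randomisation is preferred for its unpredictability, change the Sample size section instead: state 24 in total with an expected, not fixed, 12 per group, and acknowledge that arm-specific precision will vary with the split. If the list is in fact already fixed at 12/12, describe it that way.
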